**1. Statement of the question and objectives**

**Statement of the question**

The tools of breast cancer diagnosis consist of the clinical examination, radiological examinations, and the anatomopathological analysis associated with immunohistochemistry. A classification of breast tumors into subtypes allows one to better evaluate the risk of recurrence and therefore to choose the optimal adjuvant therapy for the patients. For more than 10 years, research, clinical studies and reviews have permitted one to highlight the value of the classification into intrinsic subtypes of tumors based on gene expression to better define the prognosis and therefore adapt the adjuvant therapy (Gnant, Harbeck, and Thomssen 2011; Perou et al. 2000; Sorlie et al. 2001; Hornberger et al. 2012). The genomic tests currently available are Oncotype DX®, Endopredict®, and Mammaprint. The fundamental work carried out by Perou and Sorlie (Perou et al., 2000; Sorlie et al., 2001), permitted a better understanding of breast cancer. The pathology is considered in different molecular subtypes which influence the therapeutic response and the prognosis; this approach was notably adopted during the international conference of St. Gallen in 2011. Therefore, the therapeutic indications (hormone therapy, chemotherapy, Herceptin) are adapted to the different subtypes: Luminal A, Luminal B, HER2 positive and triple negative. The Prosigna™ test (assay) by NanoString® Technologies, Inc. (Seattle, WA), measures the level of expression of 50 genes from the tissue specimens fixed in formalin and embedded in paraffin and permits the classification of the tumors into subtypes and gives a score for the risk of recurrence at 10 years. The first clinical validation study of the Prosigna™ test (assay) on 1,017 specimens and comparing the results to Oncotype DX® has highlighted a more significant prognosis power of the Prosigna™ test (assay) with a lower number of patients classified as intermediate risk (Dowsett M et al. 2011). This tool in prognosis and in helping with the therapeutic decision will soon be used in common practice. It is therefore necessary to evaluate within a controlled clinical trial the impact of the test result on the therapeutic modifications on one hand and on the feelings of the physician and the patient on the other hand.

**The primary objective** of this study is to evaluate the impact of the result of the ProsignaTM Test (assay) on the therapeutic decision of adjuvant therapy (chemotherapy and hormone therapy) in patients suffering from early-stage breast cancer. The following will be considered as therapeutic changes:

**The secondary objectives** will consist of

- The evaluation of the confidence in the therapeutic indications of the practitioners before and after the test (assay) results, and by subgroups of cancers

- The evaluation of the rate of secondary effects of chemotherapy,

- The evaluation of the emotional state of patients faced with the therapeutic decision, of their degree of anxiety and of their functional status before and after the ProsignaTM test (assay) results

**2. Study Population**

All of the patients managed consecutively in the participating centers and meeting the inclusion criteria will be offered participation in the study. The patients who are incapable of signing an informed consent form will not be included in the study.

**Inclusion criteria**

- Invasive early-stage breast cancer (T1-T2, N0, pN0(i+), pN0 (micro-metastatic), M0), operated on immediately, with positive estrogen receptors, non-overexpressed HER2
  - The status of the hormonal receptors in the estrogen will be evaluated by immunohistochemistry. A fixation of more than 1% of the cells will be considered as positive.
  - The HER2 status will be evaluated by immunohistochemistry (IHC) and/or fluorescence in situ hybridization (FISH). (0 or 1+ or 2+ in IHC will be considered as negative in the absence of FISH).
- The patients must be post-menopausal. The "post-menopausal" status will be defined by:
  - Amenorrhea for more than 12 months, regardless of the age
  - Medical history of bilateral ovariectomy (oophorectomy) (surgery carried out, at the minimum, 4 weeks before the inclusion), regardless of the age
  - Radiological castration (cessation of ovarian function) with amenorrhea for more than 3 months, regardless of the age
  - Medical history of hysterectomy with hormonal biological doses in favor of menopause.
- Patient capable of giving her consent
- Patient eligible for therapy through adjuvant chemotherapy
- ECOG score of 0 or 1

**Exclusion criteria**

- Tumor size T3-T4
- Non-invasive breast cancer (CIS, Paget.)*
- Nodal status other than N0, pN0 (i+), or pN0 (mol+)
- Tumor that is estrogen-receptor negative or has overexpressed HER2
- Metastasis
- Patient incapable of giving her consent
- Patient incapable of filling out the questionnaires
- Contraindication to chemotherapy
- ECOG Score >1

**Recruitment and inclusion of patients**

The patients will be informed by the investigator of the terms of the study and of the legal provisions of a clinical research study. They will receive a written letter of information (presented as an appendix). The patients, at any time during the study, will be able to contact the investigator for additional information. The contact details of the investigators will be shown on the information letter. The patients will sign an informed consent form in duplicate giving their agreement for a 6 month follow-up and the use of their tissue specimen for future studies. The patients will be included in different centers, and no centers will be represented disproportionately. The informed consent form will be sent to the Institut Curie for review. In case of refusal of participation of a patient, the consultation date and the reasons for refusal will be documented. To complete the inclusion of a patient, the investigator will connect to a secure site using a personal login and password. The inclusion instructions will be available on the site.

The number of patients to be included is 200.

**Training of investigators**

The Institut Curie will coordinate the contacts with the investigators of each center and will provide the training of the investigators concerning the inclusions, the terms of the study and the informed consent forms.

NanoString Technologies will provide the training of the anatomic pathology laboratories of each center and will provide them with a written protocol explaining the preparation of the specimens necessary for the completion of the test (assay).

The tests (assays) will be carried out on the genomic platform of the Institut Curie in Paris and at the Centre Jean Perrin in Clermont-Ferrand. The members of these laboratories have already been trained in the performing of the ProsignaTM tests (assays) using the NanoString nCounter technology. Internal controls will be organized regularly within the platform.

**3. Methodology**

This is a French multicenter prospective study.

**Data anonymization**

The information concerning the patients will be kept strictly confidential. Before data collection in the eCRF, the patients will be de-identified and an identification number will be assigned to them. The anonymization number (3 digits) will correspond to the participating center for the first digit and in the order of the consecutive inclusion of the patient of each center. The list of the identification numbers linked to the patient identities will be kept by the principal investigator of the center in the investigation file.

**Performing the ProsignaTM genomic test (assay)**

The ProsignaTM genomic test (assay) will be carried out on the surgical specimens of patients who have agreed to participate in the study, within the genomic platform of the Institut Curie. The test results will be expected within 7-10 days.

The anatomic pathology laboratory of each center trained on the study, once it has the informed consent form, will be in charge of the preparation of the specimen and for the delivery of the specimen to the genomic platform of the Institut Curie. The anonymization number provided during the inclusion by the investigator will be reported on the specimen. This specimen will be sent by courier (FedEx ® Clinical Pack) to the genomic platform of the Institut Curie where RNA extraction and the ProsignaTM test (assay) will be carried out. The results will be transmitted to the investigator within a time period of 7-10 days in the form of a report containing the patient identification number in the study, the molecular subtype and the risk of recurrence at 10 years. These results will be available both on the secure server dedicated to the study, and linked to the patient using the patient identification number, and also transported by courier to the anatomic pathology laboratory of the center which is managing the patient.

**Gathering of data and modes of data circulation**

Once the consent form is signed and before the test results, the investigator and the patient will complete the Case Report Form (CRF), pre-Prosigna. The physician will provide the information concerning the patient and disease characteristics, and of the adjuvant therapy planned. At the inclusion visit (signing of the informed consent form), the patients will fill out pre-Prosigna questionnaires concerning their state of anxiety, the difficulties felt in face of the therapy and the quality of life. The CRFs of the study will be presented in an electronic form (eCRF). Access to the eCRF server will be secured by personal access codes provided to each investigator by the principal investigator/data manager. Each investigator will have access to the anonymized data of the patients that he or she will have included in his or her center. Access to all of the data will only be accessible to the principal investigator/data manager. This data will be stored on a secure server.

The anonymized anatomic pathology report, as well as the results from the ProsignaTM test (assay) will be collected and stored with the eCRFs.

Once the test (assay) results are obtained, the investigator and the patient will complete the post-Prosigna CRF. Information regarding the adjuvant therapy decision will be collected again, as well as the patient's state of anxiety and her difficulties felt, faced with the therapy.

During a 6 month inclusion follow-up visit, the patients will fill out the follow-up CRF in which information regarding their degree of anxiety, their possible difficulties felt facing the therapy and their quality of life will be collected. The physicians will also fill out a 6 month CRF concerning their opinion on the usefulness of the test (assay), their confidence in the test results and the patients' medical follow-up elements.

The various CRFs are shown as appendices.

**4. Creation of a specimen bank**

During this study, a breast cancer tissue bank will be formed. For each patient participating in the study, a paraffin-embedded tumor section will be sent to the Institut Curie to carry out the ProsignaTM test (assay) and may be used for future projects of translational research. The collection of tumor specimens in this study will be carried out according to the recommendations published in the “Recommendations for collection and handling of specimens from group breast cancer clinical trials” .

**5. Data analysis**

**Primary Endpoint**

Evaluation of the proportion of patients for which the therapy was modified following the results of the ProsignaTM Test (assay).

**Secondary Endpoints**

• Proportion of patients for which the therapy was modified, stratified by cancer recurrence risk group (low, intermediate, high)

• Proportion of patients for which the therapy was modified, for the sub-group of patients who have a recurrence risk close to the limits between groups (+/- 5% of the limits).

• Confidence of the practitioners in the therapeutic recommendations before and after the results from the ProsignaTM Test (assay) for each sub-group (low, intermediate and high risk of recurrence).

• Modifications of the patients' difficulties linked to the choice of therapy, of the degree of anxiety and of the functional status of the patients before and after the ProsignaTM Test (assay), stratified by the sub-groups of recurrence risk.

• Rate and severity of the secondary effects of the therapy, according to the administration or non-administration of chemotherapy.

• Agreement of the classification into molecular subtypes between the ProsignaTM Test (assay) and the immunohistochemistry.

• Retrospective research on the tissue specimens collected.

**Method of analysis**

The clinical and demographic characteristics of the inclusion population will be described by mean, median, standard deviation, range and frequencies. The proportion of patients for whom the choice of therapy from the physician has changed before and after the ProsignaTM test (assay) results will be calculated with a confidence interval of 95%. The confidence changes of the practitioners in the therapies carried out before and after the test (assay) results will be analyzed by calculating the mean (CI 95%).

**Power analysis**

In order to obtain a confidence interval of 95%, we will include 200 patients in total (all centers combined).

Table 1 Calculation of the specimen size according to the confidence interval

| Confidence interval | Proportion (P) | Lower limit | Distance from P to lower limit | | Sample size (N) |
| --- | --- | --- | --- | --- | --- |
| 0.95 | 0.25 | 0.20 | 0.05 | 200 | |
| 0.95 | 0.25 | 0.19 | 0.06 | 137 | |
| 0.95 | 0.25 | 0.18 | 0.07 | 100 | |
| 0.95 | 0.25 | 0.17 | 0.08 | 76 | |
| *References: Fleiss, J. L., Levin, B., Paik, M.C. 2003. Statistical Methods for Rates and Proportions. Third Edition.*  *John Wiley & Sons. New York. Newcombe, R. G. 1998. 'Two-Sided Confidence Intervals for the Single Proportion:*  *Comparison of Seven Methods.' Statistics in Medicine, 17, pp. 857-872.* | | | | | |

Figure 1 Sample size depending on the confidence interval

[figure not shown]

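### Table 1's sample sizes match a one-sided 95% exact lower bound, not the 95% confidence interval they are labelled as, so the stated precision at 200 patients is 0.5 to 1 point too favourable

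*Protocol*

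**What the plan says.** The sample size rests on one sentence under Power analysis in Section 5 of the protocol, "In order to obtain a confidence interval of 95%, we will include 200 patients in total (all centers combined", and on Table 1 beneath it. The table's columns are the confidence level, the proportion P, the lower limit, the distance from P to that limit, and N. The row that gives the trial its size is "0.95 | 0.25 | 0.20 | 0.05 | 200". The other rows are "0.95 | 0.25 | 0.19 | 0.06 | 137", "0.95 | 0.25 | 0.18 | 0.07 | 100" and "0.95 | 0.25 | 0.17 | 0.08 | 76".

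The table shows no upper limit, names no interval method and does not mention a one-sided bound. One of its two references is a comparison of methods whose title begins "Two-Sided Confidence Intervals for the Single Proportion".

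Under Method of analysis, the proportion of patients whose treatment choice changed "will be calculated with a confidence interval of 95" per cent. The primary endpoint is that single proportion.

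**The concern.** An unqualified 95% confidence interval for a proportion is normally read as two-sided, and the cited title points the same way. A quick normal-approximation check at P = 0.25 and N = 200 gives a two-sided half-width of 0.060, whereas the table states 0.05. The one-sided multiplier gives 0.0504. This suggests that the sizing and the planned analysis use different tail areas.

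Table 1 is the protocol's only numerical justification for 200 patients. If it was built on 5% in the lower tail and the result is reported with 2.5% in each tail, then an observed change rate of exactly 25% will come with a lower limit below the tabulated 0.20.

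**Working it through.** **Inputs.** P = 0.25; lower limits 0.20, 0.19, 0.18 and 0.17; N = 200, 137, 100 and 76 (all from Table 1). The confidence level is 0.95 (Table 1 and Method of analysis). Sidedness is not stated, so both are tried: z = 1.645 one-sided, z = 1.960 two-sided.

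**Formulas for the lower limit**, with x = N × P:
- Wald: P − z √(P(1 − P)/N).
- Wilson: [2NP + z² − z √(z² + 4NP(1 − P))] / [2(N + z²)].
- Exact (Clopper-Pearson): the α quantile of a Beta(x, N − x + 1) distribution, with α = 0.05 one-sided and 0.025 two-sided. Where x is not a whole number, the formula is applied as it stands.

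**Step 1: reproduce the table.** The smallest N whose lower limit reaches the stated value is:

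| Method | 0.20 | 0.19 | 0.18 | 0.17 |
| --- | --- | --- | --- | --- |
| Table 1 | 200 | 137 | 100 | 76 |
| Exact, one-sided 95% | 199 | 137 | 100 | 76 |
| Wald, one-sided 95% | 203 | 141 | 104 | 80 |
| Wilson, one-sided 95% | 174 | 116 | 82 | 60 |
| Exact, two-sided 95% | 276 | 190 | 137 | 104 |
| Wilson, two-sided 95% | 246 | 165 | 116 | 85 |
| Wald, two-sided 95% | 289 | 201 | 147 | 113 |

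The one-sided exact bound gives three rows to the patient and the first within one patient. At the tabulated N its values are 0.2002, 0.1900, 0.1802 and 0.1703. No two-sided row matches. Continuity-corrected versions do not match either: two-sided, they need 308/217/161/125 (Wald) and 266/181/130/97 (Wilson).

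As a hand check on the two-sided Wald figure for the first row: N = 1.96² × 0.25 × 0.75 / 0.05² = 3.8416 × 0.1875 / 0.0025 = 288.12, so 289.

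**Step 2: what 200 patients give under the planned analysis.** For 50 of 200, two-sided 95%:

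| Method | Interval | Distance from 0.25 to lower limit |
| --- | --- | --- |
| Exact | 0.192 to 0.316 | 0.25 − 0.1916 = 0.0584 |
| Wilson | 0.195 to 0.314 | 0.25 − 0.1951 = 0.0549 |
| Wald | 0.190 to 0.310 | 0.25 − 0.1900 = 0.0600 |

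Against the tabulated 0.20, the lower limit is short by 0.20 − 0.1951 = 0.005 (Wilson), 0.20 − 0.1916 = 0.008 (exact) and 0.20 − 0.1900 = 0.010 (Wald).

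**Step 3: what an unrounded two-sided lower limit of 0.20 would take.** 246 (Wilson), 276 (exact) or 289 (Wald) patients, that is 46, 76 or 89 more than planned.

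**The case against.** **Sidedness is inferred.** The protocol's own prose says neither one-sided nor two-sided. The term two-sided appears only in the title of a cited paper. A table that lists lower limits and no upper limits may have been meant as a lower-bound table. That is a fair reading and fits the numbers. It does not remove the mismatch, because the label says confidence interval and the planned analysis is an interval.

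**Rounding.** The table prints two decimals. The two-sided Wilson limit at N = 200 is 0.1951, which prints as 0.20. At N = 100 and N = 76 it is 0.1755 and 0.1663, which also round to the stated limits. At N = 137 it is 0.18498, which prints as 0.18 and not 0.19. Wilson with rounding therefore fits three of the four rows, and would not make N the number needed to reach the limit. The one-sided exact bound fits all four.

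**Nothing turns on 0.20.** The study is single-group and descriptive. It has no null value, hypothesis test or success rule. The 0.20 is one row of a precision table and is conditional on observing exactly 25%. With 52 of 200 (26%), the two-sided exact lower limit is already 0.2007. This objection stands, and it limits how serious the point is.

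**A later analysis plan may name the method.** It may, but it cannot make Table 1 correct for a two-sided 95% interval.

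**Conclusion.** The point holds as a should-fix error of labelling and stated precision. Table 1's figures are those of a one-sided 95% exact lower bound, equal to the lower end of a two-sided 90% interval, yet they are presented as a 95% confidence interval and support a primary result to be reported with one. The distance from P to the lower limit at N = 200 is about 0.055 to 0.060 instead of 0.05, a difference of 0.5 to 1 percentage point.

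Two stronger readings are tempting and not supported. One is that the trial is too small and must recruit 246 to 289 patients. Nothing in the protocol requires the lower limit to reach 0.20, so no conclusion of the trial depends on the shortfall. The other is that the primary analysis is wrong. The planned 95% interval is conventional and sound, and the fault lies in the table that was meant to support it.

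The conclusion assumes that the planned interval is two-sided, that all 200 patients contribute a decision before and after the test, and that 25% is observed. The one-sided origin of the table is a reconstruction from its numbers.

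**What to change.** Keep 200 patients and keep the two-sided 95% interval as the primary analysis. Do not turn the one-sided bound into the primary analysis to suit the table.

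Under Method of analysis and Power analysis, name the interval method. If the exact method is chosen, the precision statement could read: with 200 evaluable patients and an observed proportion of 0.25, the two-sided exact 95% confidence interval is 0.192 to 0.316 (lower limit about 0.19, distance about 0.06).

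Then do one of two things with Table 1:
- Correct all rows to the two-sided exact basis: N = 276, 190, 137 and 104 for distances of 0.05, 0.06, 0.07 and 0.08.
- Or relabel the table as a one-sided 95% lower bound and print the two-sided 95% interval at N = 200 beside it.

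The cost is protocol wording only. No patients are added, and the stated precision becomes about 1 point less favourable.

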**Sample size (N)**

**Confidence Interval**

**6. Monitoring of the study**

In order to assure the proper conduct of the study, each site will receive 3 monitoring visits:

**First visit**

The first visit will take place in each center after inclusion of the first 5 patients. During this visit, a reminder of the study procedures will be carried out with the center investigators. The following data will be verified for each participant:

- Informed consent form actually signed
- Inclusion and exclusion criteria
- Pre-Prosigna patient CRF (correctly filled out, actually prior to the test)
- Pre-Prosigna physician CRF (correctly filled out, actually prior to the test)

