**Second visit**

The second visit will take place in each center after inclusion of the last patient. The following data will be verified for each participant:

- Post-Prosigna patient CRF (correctly filled out, actually after the test)
- Post-Prosigna physician CRF (correctly filled out, actually after the test)

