**Third visit**

The third visit will take place in each center after the 6 month follow-up of the last patient included. The following data will be verified for each participant:

- Patient follow-up Prosigna CRF (correctly filled out, actually at 6 months)
- Physician follow-up Prosigna CRF (correctly filled out, actually at 6 months)

Any deviation from the initial protocol will be documented and submitted to the principal investigator/data manager after each visit.

Additional monitoring will be carried out if necessary.

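### Eligibility and the timing of the pre-test CRFs are checked only at the first monitoring visit, so about three quarters or more of the primary-endpoint baselines have no scheduled verification

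*Protocol*

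**What the plan says.** Section 6 of the protocol (Monitoring of the study) plans three visits per site, each with its own checklist.

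- **First visit.** "The first visit will take place in each center after inclusion of the first 5 patients". The list covers consent ("Informed consent form actually signed"), the eligibility criteria, and the pre-test patient and physician forms. The physician item reads "Pre-Prosigna physician CRF (correctly filled out, actually prior to the test)". The introduction to the list says it applies to every participant.
- **Second visit.** "The second visit will take place in each center after inclusion of the last patient". Only the post-test forms are listed. The physician item is "Post-Prosigna physician CRF (correctly filled out, actually after the test)".
- **Third visit.** Only the 6-month forms are listed. The physician item is "Physician follow-up Prosigna CRF (correctly filled out, actually at 6 months)". The section closes with "Additional monitoring will be carried out if necessary", giving no trigger or scope.

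Other sections bear on the same point. Section 3 (Gathering of data and modes of data circulation) requires the pre-test forms to be completed after consent and before the result. Section 3 (Performing the Prosigna test) says of the results: "These results will be available both on the secure server dedicated to the study". They also go by courier to the center's pathology laboratory. The text does not tie either route to completion of the pre-test form. Section 5 defines the primary endpoint as the proportion of patients whose therapy was modified after the result, obtained by comparing the physician's choice before and after the test.

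**The concern.** The study describes no control arm. Each patient's post-test decision is compared with her own pre-test plan, so the pre-test physician CRF is the whole baseline of the primary endpoint. The protocol itself treats the timing of that form as something to be verified, but verifies it at a visit that cannot see patients who are not yet enrolled. The promise to check every participant and the timing of the visit do not fit together.

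A pre-test plan written once the result is known will tend to agree with the post-test decision. A real change is then recorded as no change, and the primary proportion is pulled downward. The planned 95% confidence interval expresses sampling error only and would not show this. A baseline recorded late cannot be recovered afterwards, although a late form can at least be identified and counted if someone compares dates.

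The same gap applies to eligibility: after the early patients in each center, no scheduled visit returns to the inclusion and exclusion criteria.

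**Working it through.** **Inputs**

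- Total sample size: 200 (sections 2 and 5).
- Trigger for the first visit: 5 inclusions per center (section 6).
- Number of centers: at most 10. This is inferred from section 3 (Data anonymization), where one digit of the three-digit patient number codes the center. It would be 9 if zero is not used.
- Planning proportion 0.25, with a distance of 0.05 to the lower 95% limit (section 5, Table 1).

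**The plan's own figure.** The smallest n that keeps the lower limit within 0.05 of 0.25 is 199 with a one-sided 95% exact (Clopper-Pearson) limit and 203 with a one-sided Wald limit, against the stated 200. Two-sided limits need more (246 Wilson, 276 exact, 289 Wald). That is a separate matter; 200 is used below simply as the denominator.

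**Coverage of the first visit**

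Checked = 5 × centers; unchecked = 200 − checked.

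| Centers | Checked | Unchecked | Unchecked share |
| --- | --- | --- | --- |
| 10 | 50 | 150 | 75% |
| 9 | 45 | 155 | 77.5% |
| 5 | 25 | 175 | 87.5% |

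The unchecked share is smallest at the maximum of 10 centers. If visits ran late, coverage would rise. To reach half the trial with 10 centers, every first visit would have to wait for 10 inclusions (10 × 10 = 100).

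**Illustration of the bias.** The documents give no rate of late completion. Assume that a fraction f of unchecked pre-test forms is completed after the result and that each of these shows no change. With u the unchecked share:

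observed proportion = 0.25 × (1 − u × f)

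| f (assumed) | 10 centers (u = 0.75) | 5 centers (u = 0.875) |
| --- | --- | --- |
| 10% | 0.25 × 0.925 = 0.231 | 0.25 × 0.9125 = 0.228 |
| 20% | 0.25 × 0.85 = 0.213 | 0.25 × 0.825 = 0.206 |
| 30% | 0.25 × 0.775 = 0.194 | 0.25 × 0.7375 = 0.184 |

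The loss is about 2 points at 10% and about 4 points at 20%, both inside the planned 0.05. At 30% it is 5.6 points (10 centers) or 6.6 points (5 centers), larger than that distance.

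**After the fix.** The second visit follows the last inclusion, so adding the items there raises planned coverage from at most about 50/200 (25%) to 200/200. The sample size does not change.

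**The case against.** The case against has several parts.

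- **Consent is not left unchecked.** A reader might infer from the three checklists that nothing verifies consent from the sixth patient on. The documents do not support that. Section 2 sends the consent forms to the coordinating institute for review, with no limit to early patients, and section 3 has the pathology laboratory prepare the specimen only once it holds the form. This stands, and consent is not part of the point.
- **Other safeguards exist.** The order of events is prescribed. Inclusion precedes testing, because the inclusion number must be on the specimen, and the result then takes 7–10 days. Forms are electronic, and the principal investigator/data manager sees all data. Deviations are documented and extra monitoring is allowed. These make late forms less likely and possibly detectable, so it would be too strong to say that the plan could never reveal them. None of them, however, is a stated check of timing for every patient. Audit-trail details may sit in data-management or monitoring documents that are not shown.
- **Early, concentrated monitoring is a legitimate choice.** True in general. Here, though, the protocol says that the check covers every participant, and the item left behind is the sole comparator for the primary endpoint.
- **The size is assumed.** This also stands. The late rates are illustrative, and the assumption that every late form hides every change is a worst case. A form entered late from notes made before the result would cause no bias.
- **The visit trigger is not a cap.** Five inclusions is when the visit falls due. A later visit would see somewhat more patients, so the coverage figures are approximate.

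**Conclusion.** The gap holds as a defect in the monitoring schedule. Eligibility and the timing of both pre-test forms have a scheduled check for about 50 of 200 patients at most, leaving about 75% or more unchecked. This rests on at most 10 centers, inferred from the numbering scheme, and on first visits taking place near the stated trigger. With fewer centers the unchecked share is larger.

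The consequence for the primary proportion is a risk of downward bias, not a demonstrated one. The fall from 25% to about 23% or 21% depends on assumed late rates of 10% and 20% and on late forms hiding every change.

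A reader might go further and conclude that the report must be withheld until the pre-test form is locked, or that the primary analysis must be confined to patients with a verified earlier form. Neither is needed. The first could delay information used in a treatment decision. The second would reduce the denominator and select patients by their physician's record-keeping. The point is a cheap improvement to a visit that is already planned.

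**What to change.** Add to the second-visit checklist in section 6, for all patients not checked at the first visit:

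1. the inclusion and exclusion criteria;
2. both pre-test CRFs (patient and physician), comparing the completion date with the date on which the result was released.

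Report the number of pre-test CRFs completed after the result. Keep all patients in the primary analysis, and give the primary proportion again without the late forms as a sensitivity analysis.

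The cost is a longer second visit. No visit is added, and the sample size and the flow of results to the centers stay as they are. The second visit comes too late to correct a late form, so the change detects and quantifies the problem but does not prevent it.
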